### Survey battery

Data on proposed demographic covariates of PA (e.g., gender, race, etc.) will be collected in the W1 survey battery [35]. Anthropometric data will be assessed by asking each participant their height and weight in the W1, W2, and W3 survey battery. The inclusion of the instruments (e.g., self-efficacy) is consistent with the previous FFW intervention research [46, 49].

### Self-efficacy to engage

After completion of the introductory challenges, PAS participants will be asked at W2 to respond to a newly developed scale designed to measure self-efficacy to engage. The 7-item scale is developed for this study based on literature pertaining to engagement with online behavioral interventions [50]. For example, the scale includes the following item: *How confident are you in your current ability to complete at least 24 post-introductory challenges in this online intervention within a 4-week time period?* Completing at least 24 post-introductory challenges within the next four weeks will be used to measure self-efficacy to engage based on substantive concerns (e.g., 2 h to complete at least 24 post-introductory challenges). A five-category rating scale structure was used for this item (i.e., 0 = no confidence to 4 = complete confidence), based on effective self-efficacy rating scale structures [51].

### PA self-efficacy

The PA self-efficacy will be measured from participants at W1, W2, and W3 with the PA self-efficacy scale [52]. The 48-item scale is a modified version of the exercise self-efficacy scale [53]. The PA self-efficacy scale was tailored for the PA context to assess the extent to which individuals believe that they have the ability to engage in a recommended amount of weekly PA for health. The scale measures weekly PA self-efficacy across the four PA domains (e.g., work-related PA). Each of the four domains has two unique stems that reference six increasing time periods.

### Self-efficacy to regulate PA

Self-efficacy to regulate PA will be measured from participants at W1, W2, and W3 with the self-efficacy to regulate PA scale [54]. The 13-item scale is a modified version of the barriers self-efficacy scale [55]. The self-efficacy to regulate PA scale was tailored for the PA context to assess the extent to which individuals believe that they have the ability to overcome possible barriers to engagement in a recommended amount of weekly PA for health. Specifically, the self-efficacy to regulate PA scale measures self-efficacy to regulate: (a) barriers to PA participation based on social considerations (e.g., one’s perception of another person’s evaluation of them like physical appearance) and (b) barriers to PA participation based on an internal subjective evaluation (e.g., an assessment of the ideality of the weather conditions).

### Acceptability of the PAS intervention

The acceptability of the PAS intervention will be assessed with PAS participants’ engagement data at W2. Consistent with the conceptualization of engagement with online interventions [50], both engagement behavior and subjective experience in the PAS intervention will be used to assess the acceptability of the intervention. Engagement behavior in the PAS intervention will be assessed at W2 by logging the number of post-introductory challenges completed by PAS participants from the PAS website. Subjective experience in the PAS intervention will be assessed by PAS participants at W2 with a modified questionnaire used in previous research [56]. The 16-item intervention acceptability questionnaire consists of a mix of 15 quantitative items with Likert-scale (i.e., 0 = strongly disagree to 4 = strongly agree) and one open-ended qualitative item.

### Acceptability of accelerometer-based assessment of PA

The acceptability of accelerometer-based assessment of PA will be assessed with a questionnaire used in previous research [46] at W1 and W3. The 11-item assessment acceptability questionnaire consists of a mix of six quantitative items with Likert-scale (e.g., 0 = strongly disagree to 4 = strongly agree) and five open-ended qualitative items.

### PA monitoring

Within 7 days after the W1 and W3 survey battery, participants will be asked to enter a code into the PAS intervention website in order to start wearing a PA monitor for the next consecutive 7 days. They will be instructed to wear a nylon belt around their waist with an accelerometer attached to it. Research staff will prepare the PA monitor package and meet each participant in the waiting room at the center to deliver the package by making an appointment. Along with a PA monitor attached to a belt, a cover letter, wear instructions, and a daily log sheet regarding wear time, will be included in the PA monitoring package. The cover letter will guide participants to use their login credentials on the PAS intervention website to enter a code to start wearing a PA monitor for the next consecutive 7 days. The wear instructions will provide full instructions with texts and pictures on how to complete the W1 and W3 PA monitoring. On the day after a 7-day interval, participants will receive a reminder by email and/or phone that prompts to use their login credentials on the website to complete instruments designed to measure the acceptability of accelerometer-based assessment of PA and self-reported PA.

Upon return of the monitor, data will be downloaded using a standard universal serial bus port. Within a few weeks of the return of the monitors, participants who provide usable data (to be described in the ActiGraph wGT3X-BT section) will be emailed a preliminary estimate of their wear time and average minutes per day of Moderate to Vigorous Physical Activity (MVPA) in relation to broad categories of recommended MVPA per week (i.e., 21.36 min/day or more). Participants who do not provide usable data will be informed that their average minutes per day of MVPA cannot be estimated due to insufficient data.

### ActiGraph wGT3X-BT

The ActiGraph wGT3X-BT (Pensacola, FL, USA) is a tri-axial research-grade accelerometer that will be used to measure PA objectively. ActiGraph devices have been used extensively as a reference device to measure free-living PA in adults [57]. Monitors will be initialized to collect raw acceleration data at 30 Hz using ActiLife software (v6.13.4). After download, data will be reintegrated to 60-s epochs. Non-wear time will be defined as ≥ 90 continuous minutes of zero counts, with allowance for 2 min of acceleration which are preceded and followed by at least 30 min of continuous zeros [58]. Usable data will be defined as follows: (a) a monitor is worn for at least 4 days including one weekend day with at least 10 h of valid wear time per day, (b) there is no evidence of monitor error, and (c) there is no issue from data compared to a log sheet. Unusable data will be treated as missing data. Average minutes per day of MVPA will be calculated based on established cut points (e.g., > 1952 counts per minute) [59].

### Self-reported PA

Self-reported PA will be measured with the long form of IPAQ [60]. This questionnaire purports to measure PA in the four domains according to the intensity, frequency, and duration of the PA performed in each domain during the previous week. Average minutes per day of MVPA will be calculated based on the IPAQ guidelines [61]. Self-reported PA will be included in the study because of the possibility of the inclusion in a definitive RCT with a large sample.

### Data analysis

Data analyses will include both quantitative and qualitative approaches. Quantitative analyses will be performed in M*plus* 8.0 under maximum-likelihood estimation with robust standard errors [62]. Missing data will be modeled under the assumption of missing at random [63]. Qualitative feedback will be summarized based on themes that emerge from the research team’s analysis. The threshold values for the traffic light system described in the feasibility outcome section will be used to evaluate results of specific indicators within each specific aim and with regard to the feasibility of a future definitive RCT. More specifically, descriptive statistics will be used to determine the feasibility of implementing the PAS intervention and the acceptability of implementing the PAS intervention. Intention-to-treat approach will be used to provide the preliminary effect size estimates [64]. The covariates, the outcome at W1, and group assignment will be specified as predictors in the approach.

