### Randomization

Thirty participants will be randomly assigned to the PAS group or the Usual Care (UC) group to achieve a 1:1 group assignment. The randomization will be performed by the PAS intervention website (i.e., computer-generated random numbers). Neither participants nor the research staff will know which group a participant will be assigned into.

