#### Participation rate

Participation rate at wave W, where W = W1 or W2 or W3, will be defined as the percentage of consented patients who provide usable data (e.g., non-missing data) at wave W: (*n*_usable data at wave W_/*n*_consent_) × 100. The lower bound threshold is < 50%. The upper bound threshold is ≥ 70%.

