### Qualitative acceptability of accelerometer-based assessment of PA

Qualitative themes that emerge from a response to qualitative items designed to assess the acceptability will be analyzed at wave W, where W = W1 or W3. The lower bound threshold is the presence of at least one potentially serious problem that is unable to be addressed in a future study. The upper bound threshold is the absence of the potentially serious problem.

### Aim 3

The Aim 3 is to provide a preliminary effect size estimate for each direct effect depicted in the conceptual model (see Fig. 1) for the PAS intervention. The preliminary effect size estimate for the direct effect of PAS to accelerometer-based assessment of PA will be the primary outcome in Aim 3. There will be secondary feasibility outcomes (e.g., PAS self-efficacy, self-efficacy PA) in Aim 3. The secondary feasibility outcomes in Aim 3 may provide additional information regarding the mechanism of the PAS intervention aimed at promoting PA. The preliminary effect sizes for each direct effect of being assigned to the PAS intervention at wave W, where W = W2 or W3 will be estimated. The lower bound threshold is < 0.00. The upper bound threshold is ≥ 0.20.

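### Robust maximum-likelihood standard errors in at most 30 people will understate the uncertainty of the Aim 3 arm effects, moderately with few covariates and more with several

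*Protocol article*

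**What the plan says.** The Data analysis section fixes the estimator: quantitative analyses run in Mplus "under maximum-likelihood estimation with robust standard errors". It also fixes the form of the effect-size model: "The covariates, the outcome at W1, and group assignment will be specified as predictors in the approach". The covariates are described only under Survey battery, as an open list: "Data on proposed demographic covariates of PA (e.g., gender, race, etc.) will be collected in the W1 survey battery". Their number is not stated.

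The sample is small: "Thirty participants will be randomly assigned to the PAS group or the Usual Care (UC) group to achieve a 1:1 group assignment", so about 15 per arm. Participation is rated green when at least 70% of those who consent give usable data at a wave, which is 21 of 30. On missing data the plan says: "Missing data will be modeled under the assumption of missing at random".

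The Aim 3 traffic light acts on the effect estimate alone: "The lower bound threshold is < 0.00. The upper bound threshold is ≥ 0.20". The article states no confidence interval, p-value or alpha, although the Methods paragraph of the Abstract does say that inferential models will be used.

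**The concern.** Three features of large-sample robust maximum likelihood push in the same direction in a small trial:

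- The maximum-likelihood residual variance divides by n and not by the residual degrees of freedom.
- The sandwich variance is biased downwards when n is small.
- Wald limits use 1.96 where a t quantile is needed.

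Each added covariate uses up a degree of freedom and makes the first two worse.

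At stake is the error bar around the arm effects (PAS to physical activity and PAS to self-efficacy). These estimates are meant to inform the definitive trial. Because the traffic light ignores sampling error, the reported standard error or interval is the reader's main guard against over-reading a value of 0.20 or more. An error bar that is too short weakens that guard.

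**Working it through.** The plan gives no interval, standard error or power figure, so there is nothing of its own to reproduce. The check is of how the stated method behaves at the stated sample size.

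**Inputs from the article:** N = 30, 1:1 (Randomization); 0.70 × 30 = 21 usable records (Participation rate); predictors are group, the W1 outcome and k further covariate terms (Data analysis).

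**Assumptions:** k is not stated, so a range of 0 to 5 is shown. A covariate with several categories, such as race, can use several terms. The correlation between baseline and follow-up is 0.6. The analysis is complete-case. Limits are normal (1.96), because no small-sample correction is named.

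**Step 1, closed form without the sandwich.** With df = n − 3 − k, the width of the maximum-likelihood interval relative to the t interval is 1.96 × √(df/n) / t(0.975, df).

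- n = 30, k = 2: df = 25; 1.96 × √(25/30) / 2.060 = 1.96 × 0.913 / 2.060 = 0.87.
- n = 21, k = 4: df = 14; 1.96 × √(14/21) / 2.145 = 1.96 × 0.816 / 2.145 = 0.75.

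Most of the shortfall therefore comes from the missing degrees-of-freedom correction and the normal quantile.

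**Step 2, simulation with the sandwich.** There were about 8,000 trials per setting, with normal errors. The outcome was regressed on group, W1 and k covariates. The sandwich variance with 1.96 was compared with the least-squares t interval.

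| n | k | Coverage, robust ML | Width relative to t interval |
|---|---|---|---|
| 30 | 0 | 92.5% | 0.90 |
| 30 | 2 | 91.3% | 0.86 |
| 30 | 4 | 89.2% | 0.82 |
| 30 | 5 | 88.5% | 0.80 |
| 21 | 0 | 91.3% | 0.86 |
| 21 | 2 | 88.5% | 0.79 |
| 21 | 4 | 85.1% | 0.73 |
| 21 | 5 | 83.5% | 0.69 |

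Monte Carlo error is about √(0.9 × 0.1 / 8000) = 0.3 percentage points. The t interval covered about 95% in every row. Skewed errors moved the robust coverage by only about 1 to 2 points.

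**Step 3, what this does to a reported interval.** In units of the outcome SD, the t-based half-width is 0.66 at n = 30, k = 4 and 0.86 at n = 21, k = 4. The robust version would show about 0.66 × 0.82 = 0.54 and 0.86 × 0.73 = 0.63.

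**The case against.** The strongest reply is that the article promises no interval. Aim 3 offers a preliminary estimate, the sample size section disclaims power, and the red and green rule looks only at the point estimate. This stands as a limit on the consequence: no traffic-light result changes. It does not remove the point. Robust standard errors have no use except to express uncertainty, and the Abstract commits to inferential models, so some measure of uncertainty can be expected beside these estimates.

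A second reply is that the covariate count and the interval method belong in a fuller document. This stands in part. The missing count is not itself criticised here, and a small-sample correction may be specified elsewhere. The estimator, however, is stated in the article, and it is the estimator that performs poorly at this size.

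Third, the results in the table depend on n and k. The figure n = 21 is the protocol's own green-light level, not a planned analysis size. The self-efficacy effects rest on surveys, so they may keep more people than the accelerometer outcome does.

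A reader might also infer that anyone without usable W1 monitor data drops out of the analysis because W1 is a predictor. The article does not support that. The loss occurs only if W1 is not itself modelled, and the text says that missing data will be modelled under missing at random without saying how W1 enters.

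Finally, even a correct half-width of 0.6 SD or more is far larger than the 0.00 to 0.20 gap between red and green. For Aim 3 that limit matters more than the choice of standard error.

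**Conclusion.** The point holds in a moderate form. As stated, and with normal limits, the method gives nominal 95% intervals for the arm effect that cover about 91 to 92.5% (0 to 2 covariates) or 88 to 89% (4 to 5) at n = 30. At n = 21 the figures are about 89 to 91% and 83 to 85%. Widths fall short of the t interval by 10 to 20% and 14 to 31%. This rests on normal limits, a complete-case model, a baseline correlation of 0.6 and the assumed range of k. Full-information likelihood may differ slightly, but it relies on the same large-sample theory.

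Two stronger readings are tempting. One is that the intervals are far too narrow. With few covariates at n = 30 the shortfall is only 10 to 14%, and the severe figures need covariate counts or data losses that the article does not state. The other is that effects would look established when they are not. The article sets no significance rule, and its decision rule uses the point estimate, which the choice of standard error does not change.

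**What to change.** For the arm effects (PAS to physical activity and PAS to self-efficacy), report intervals from a small-sample method. Two options are suitable:

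- ANCOVA on the W1 outcome with residual-degrees-of-freedom variance and t limits.
- A repeated-measures model fitted by REML with Kenward-Roger degrees of freedom. Treating W1 as an outcome in this model also settles how people without usable W1 data are handled under missing at random.

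Name the covariates in advance and keep them few. The calculations show a steady cost per added term but do not establish a particular maximum.

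The arm-effect model does not estimate the other paths in the conceptual model, such as self-efficacy to physical activity. If Mplus is kept for those, say that their standard errors are large-sample approximations, or use a bootstrap or small-sample-corrected interval.

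The cost is analysis wording, a second procedure for the arm effects and wider reported intervals. Recruitment, conduct and data collection do not change.

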## Discussion

We believe that the PAS intervention may have the potential to be effective in promoting PA in adults with obesity because of the three following reasons. First, the PAS intervention is based on self-efficacy theory to address the unique barriers to PA in adults with obesity [32–37]. Instead of typical PA advice, effective behavioral change techniques for the promotion of PA in adults with obesity are used in the PAS intervention based on previous research [23–25]. Second, a research-grade accelerometer is included in the implementation of the PAS intervention for the accurate evaluation of the program. This is important because recent findings reported less than high agreement in estimates of PA between accelerometer-based and self-report assessments [65]. Third, the implementation of the PAS intervention is in line with recent recommendations by the Community Preventive Services Task Force [66]. To be specific, implementing the PAS intervention includes activity monitors and promotes PA within a more broadly focused weight management program where there is access to a health care provider.

We are aware of at least three limitations for the feasibility study described in this protocol. The first limitation is that the recruitment of participants is to occur within a relatively controlled local context. Future research that investigates the feasibility and acceptability of implementing the PAS intervention for adults with obesity in a less controlled context (e.g., recruitment via a national health care panel recruitment company) may be worthwhile given the scientific utility of evaluating interventions in a variety of contexts [67, 68]. The second limitation is that each participant will be determined to be eligible for this study based on self-report. For some eligibility criteria (e.g., BMI), this limitation may be relatively minor due to a structural characteristic of the study design. For example, the eligibility criterion that BMI ≥ 25.00 kg/m^2^ should be truly met because enrollment in the weight management program provided by the center requires at least BMI ≥ 30.00 kg/m^2^. However, for some eligibility criteria (e.g., age), this limitation should be potentially more problematic due to the absence of a structural characteristic in the study design that can prevent the provision of false information. The third limitation deals with some uncertainty regarding the qualitative approach in aim 2. Although the qualitative approach (i.e., open-ended questions) in aim 2 to assess the acceptability of implementing the PAS intervention represents an extension of a more quantitatively focused questionnaire used in this study, it may still fail to collect some important information that a more rigorous qualitative approach (e.g., in-depth interviews) would provide.

Research suggests that adults with obesity should increase health-enhancing physical activity. We believe that an intervention for this important behavior change should be specifically developed based on evidence-based behavioral science and implemented with the use of technology and in collaboration with an external community partner. Results from the feasibility study described in this protocol are intended to inform the preparation of a future definitive RCT.

## Data Availability

Not applicable.

## Abbreviations

BMI: Body mass index
FFW: Fun for wellness
PA: Physical activity
PAS: Physical activity self-efficacy
SPIRIT: Standard protocol items: recommendations for interventional trials
UC: Usual care
USA: United states of America
W1: Wave 1
W2: Wave 2
W3: Wave 3
